### Participant eligibility

Patient and clinician eligibility criteria are shown in Table 2. Patient eligibility is determined by the Research Assistant reviewing clinicians’ schedules with a checklist of inclusion and exclusion criteria. If eligibility is uncertain, the Research Assistant checks with office staff. Patients are excluded if they are deemed inappropriate for participation due to an acute or unstable medical condition or if they are unable to provide informed consent due to a language barrier, limited literacy, and/or cognitive concerns.

**Table 2 T2:** Inclusion and exclusion criteria

	**Inclusion criteria**	**Exclusion criteria**
Patients	**·** Currently enrolled patients at Westside Health Services, Inc.)	**·** Have a life-threatening or acute medical problem which precludes participation
	**·** Scheduled for a routine, follow-up, or health maintenance office visit	**·** Unable to read and understand English
	**·** Scheduled to see a participating clinician	
	**·** 18 years of age or older	
	**·** Able to provide written informed consent	
	**·** Have one or more stable medical conditions for which activity is not contraindicated (e.g., asthma, patients undergoing chemotherapy, diabetes, hypertension, stable cardiovascular, neurological, or psychiatric disease)	
Clinicians	**·** Practicing clinicians (physicians, physician assistants, or nurse practitioners) at community health center organization	**·** Planning to move or relocate to another practice in the study period
		**·** Serving as study investigators or advisors

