### Recruitment of clinician participants

The principal investigator presents an overview of the study’s objectives, design, and time frame to eligible clinicians at a weekly clinician meeting. Each clinician’s full participation requires the clinician to 1) complete a 10 minute written baseline assessment, 2) attend four one-hour training sessions held during regularly scheduled provider meeting times over a four-month period, 3) consent to having 10 patient visits audio-recorded at baseline and 15 at post-intervention, and 4) complete a post-intervention survey and a 20 minute individual interview. Based on estimates from a previous pilot project, we anticipate a 10 patient visits at baseline should be sufficient; however, if the visits do not contain any discussions of physical activity, clinicians are told that the baseline assessment may consist of > 10 visits. In addition to clinicians’ informed consent, research staff explain that patient informed consent is obtained prior to any recording. For patients providing informed consent, an audio-recorder is placed unobtrusively in the exam room. Each clinician receives $60 per completed hour of the four hours of training and $5 per recorded visit. The principal investigator also explains the overall goals and procedures of the study to all clinical staff at their regularly scheduled team meetings. Staff are encouraged to forward any inquiries from patients about the study to members of the study team. The clinical practice receives a $2000 stipend for use of the facility and staff time. Clinician participants then provide written informed consent.

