### Procedure for randomization

A concealed randomization procedure stratified by health center location and clinician type (physician, nurse practitioner, or physician assistant) is used to balance randomization between both groups. A series of treatment assignments in a block of five is generated by the study statistician in advance of the intervention and placed in a file accessible to the Research Assistant responsible for administering the group assignment to each clinician. Clinicians are notified of their randomization assignment by the Research Assistant immediately after providing informed consent by opening a sealed envelope with the assigned intervention category for each individual: Group 1 (Early) or Group 2 (Wait-list). Neither study clinicians nor research staff are blind to the assignment of clinicians to the early or wait-list training groups.

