### Clinician baseline assessment

Prior to the training intervention, clinician participants from both groups complete a baseline assessment consisting of (1) a brief survey to obtain baseline demographic information, experience and confidence with physical activity counseling, attitudes and beliefs about incorporating it into their practice, and knowledge of community resources for physical activity for their patients, and (2) a baseline assessment of 10 audio-recorded office visits.

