### Patient participant recruitment and enrollment

When potentially eligible patients enter exam rooms for their visit, a nursing assistant mentions the project to see if they might be interested in participating. The Research Assistant then obtains written consent from eligible and interested patients. As part of the informed consent process, patients are told that they are not obliged to deliberately discuss physical activity. The visit is then audio-recorded. As with the clinician informed consent procedure, patients are explicitly informed that if they agree to participate, the recorder is placed unobtrusively in the exam room. The consent process takes about five minutes and is designed for minimal disruption of office flow and schedules. Patients are recruited until there is adequate baseline information about physical activity discussions.

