### Patient post-visit survey

After the recorded visit, a brief face-to-face survey is administered to the patient participants. Items include socio-demographics data (age, gender, marital status, race and ethnicity, highest educational level attained, and insurance status), the SF-12, and other measures described in (sections Evaluation and measures and Exploratory outcome measures). The survey takes about 15 minutes. Patients then complete a 5–10 minute interview asking about their perspective on the content, adequacy, and clarity of communication about physical activity counseling.

Patients are compensated a total of $20 ($10 for participating in the audio recording portion and $10 for their time completing the survey and interview).

After the baseline assessment is completed for Group 1 clinicians and their corresponding patients, Group 1’s training intervention begins.

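### Clinicians and recruiting staff know the allocation before any baseline visit is recorded, so baseline is not protected against group differences that arise before training

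*Protocol article*

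**What the plan says.** **Order of events.** Under Recruitment of clinician participants, taking part requires each clinician to "consent to having 10 patient visits audio-recorded at baseline and 15 at post-intervention". Under Procedure for randomization, "Clinicians are notified of their randomization assignment by the Research Assistant immediately after providing informed consent", by opening a sealed envelope. The Clinician baseline assessment section then says that "clinician participants from both groups complete a baseline assessment", made up of a survey and 10 recorded visits. Under Patient post-visit survey, Group 1 training starts "After the baseline assessment is completed for Group 1 clinicians and their corresponding patients".

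**Who knows.** The randomization section adds: "Neither study clinicians nor research staff are blind to the assignment of clinicians to the early or wait-list training groups". The role that hands out the assignments also screens patients ("Patient eligibility is determined by the Research Assistant reviewing clinicians’ schedules", under Participant eligibility) and obtains their consent.

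**Length of baseline.** The recruitment section says that "if the visits do not contain any discussions of physical activity, clinicians are told that the baseline assessment may consist of > 10 visits". The section on patient recruitment is broader: "Patients are recruited until there is adequate baseline information about physical activity discussions".

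**Use of baseline.** Under Statistical analyses, H1 compares post-intervention recordings with baseline, and the primary mixed model has the baseline 5A score as a fixed effect.

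**The concern.** A baseline taken before allocation is known can differ between arms only by chance. Here Group 1 clinicians know during baseline that training is close, and Group 2 clinicians know they will wait. Either group might raise or hold back talk about physical activity in response. The staff who choose and consent patients have the same knowledge. A resulting group difference at baseline would pass into any change from baseline, and through the covariate into the adjusted comparison of groups. With at most 15 clinicians, a few affected baselines would carry weight.

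A smaller concern is the extension rule. Whether baseline continues depends on whether physical activity has come up, and clinicians are told so. That tells them which topic the recordings are waiting for.

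**Working it through.** **1. Sequence.** No figure in the article is in dispute here, so the main check is to set the sections side by side.

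- Recording is one of the things consented to, so it cannot come before clinician consent.
- Disclosure is immediate on consent.
- Baseline is described as done by clinicians of both groups, and Group 1 training follows it.

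The order is consent, disclosure, baseline, training. No section gives another order.

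**2. What a baseline shift would do (illustration).** The article gives nothing from which to estimate a shift, so assume that knowledge of allocation moves one group's baseline mean by *b* and leaves later scores alone.

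- A change-score contrast moves by *b*.
- A baseline-adjusted contrast moves by about *b* × *R*. Here *R* = *m*·ICC / (1 + (*m* − 1)·ICC) is the reliability of a clinician's baseline mean, assuming clinicians' underlying levels are otherwise stable.
- With *m* = 10 visits (from the article) and assumed ICCs:
  - ICC 0.05: *R* = 0.50/1.45 = 0.345
  - ICC 0.10: *R* = 1.00/1.90 = 0.526
  - ICC 0.20: *R* = 2.00/2.80 = 0.714

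| Assumed *b* | Change-score contrast moves | Adjusted contrast moves (ICC 0.05 to 0.20) |
|---|---|---|
| 0.1 | 0.10 | 0.03 to 0.07 |
| 0.2 | 0.20 | 0.07 to 0.14 |
| 0.3 | 0.30 | 0.10 to 0.21 |

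The planned detectable difference is 0.54 (Sample size and power). For *b* = 0.2 the adjusted contrast thus moves by 0.069/0.54 = 13% to 0.143/0.54 = 26% of it. The sign follows the sign of *b*, which is unknown.

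**3. Mechanical effect of the extension rule.** Take the rule as 10 visits, then continue to the first visit with physical-activity talk.

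- Inputs: pilot mean 5A score 0.74 and SD 1.06 (Sample size and power). Assumption: the mean is over all pilot visits.
- Share of visits scoring above zero, by the Cauchy-Schwarz bound, is at least mean² / (mean² + SD²) = 0.5476 / (0.5476 + 1.1236) = 0.33. The share of visits in which the topic arises is at least as large.
- Chance that none of 10 visits is on topic, at *p* = 0.328: (1 − 0.328)^10 = 0.019, so about 2% of clinicians would be extended.
- Upward bias in the mean clinician-level proportion: 0.0189 × Σ *p*(1 − *p*)^(k−1)/(10 + k) = 0.0189 × 0.0788 = 0.0015. Relative to 0.328 this is 0.45%.
- Pooled over visits, with *p*₀ = (1 − *p*)^10, expected on-topic visits over expected visits is (10*p* + *p*₀) / (10 + *p*₀/*p*) = *p*. The rule therefore has no effect on that ratio.
- If the 5A score is taken only over visits where the topic is raised, the rule does not shift it, because stopping depends on whether the topic arises and not on how many As are then used.

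The 2% assumes one rate for all clinicians. An individual with a rate of 10% would be extended with probability 0.9^10 = 35%, and that clinician's expected baseline proportion would be 0.120 instead of 0.100.

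**The case against.** The strongest reply is that the disclosure effect has neither size nor direction in the article. Clinicians hear the study objectives before they consent, so much of their reactivity to being recorded would remain whatever the order of steps. Eligibility is judged by a checklist against schedules, a nursing assistant makes the first approach, and patients are told they need not raise physical activity. Recruitment after training is equally unblinded. Coders are blinded to clinician and time point, Hawthorne effects are listed as a concern to be examined, and Group 2 has a second assessment before its own training that gives a partial check on drift.

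Most of this stands as a limit on how much can be claimed. It does not remove the point. Blinded coding protects the scoring, not the clinician's behaviour or the choice of patients. General reactivity affects both groups, whereas disclosure adds a possible difference between them. The interviews and the second Group 2 assessment come too late to restore a baseline free of knowledge of allocation.

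A reader might also infer that the extension rule seriously inflates baseline. The documents do not support that. Average discussion rates low enough to produce a large inflation do not fit the pilot mean and SD if that mean is over all visits. If scores are taken over on-topic visits only, the rule does not shift them. Any mechanical effect raises baseline and so works against H1. Nor does it follow that baseline should stop at 10 visits whatever they contain: under the on-topic definition of the score, a clinician with no such visit would have no defined baseline.

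**Conclusion.** The point holds in a limited form. The article fixes an order in which all baseline data follow disclosure of allocation to clinicians and recruiting staff, and that baseline serves both as the H1 comparator and as a model covariate. A group difference arising before training is therefore possible, and nothing in the plan prevents it.

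A reader might go further and infer that baseline is biased, or biased in favour of the intervention. The article does not show this, and it gives no basis for a size or a sign. The shifts of 0.07 to 0.14 (adjusted) and 0.2 (change score) rest on an assumed 0.2-point baseline shift in one group and assumed ICCs of 0.05 to 0.20.

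The extension rule is secondary. Its remaining risk is that clinicians are told content matters, which may cue the behaviour. On the pilot figures, read as an all-visit mean with a common rate, the sampling effect is about 2% of clinicians extended and a relative bias under 1%.

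**What to change.** Open each clinician's envelope only after that clinician's last baseline recording and survey. The assignments, which the article places in a file accessible to the Research Assistant, need to stay unseen until then. The stratified list prepared in advance can be used unchanged. The cost is shorter notice for scheduling Group 1 sessions. General reactivity to the known study aims, and unblinded recruitment after training, would remain, so the change removes one source of group difference and does not make baseline free of reactivity.

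For the extension rule, do not tell clinicians that the content of visits affects how many are recorded; they can still be told that more than 10 visits may be recorded. Analyse every recorded baseline visit, including those that led to an extension. This costs a change of wording in the clinician briefing.

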### Clinician baseline assessment

Prior to the training intervention, clinician participants from both groups complete a baseline assessment consisting of (1) a brief survey to obtain baseline demographic information, experience and confidence with physical activity counseling, attitudes and beliefs about incorporating it into their practice, and knowledge of community resources for physical activity for their patients, and (2) a baseline assessment of 10 audio-recorded office visits.

### Patient participant recruitment and enrollment

When potentially eligible patients enter exam rooms for their visit, a nursing assistant mentions the project to see if they might be interested in participating. The Research Assistant then obtains written consent from eligible and interested patients. As part of the informed consent process, patients are told that they are not obliged to deliberately discuss physical activity. The visit is then audio-recorded. As with the clinician informed consent procedure, patients are explicitly informed that if they agree to participate, the recorder is placed unobtrusively in the exam room. The consent process takes about five minutes and is designed for minimal disruption of office flow and schedules. Patients are recruited until there is adequate baseline information about physical activity discussions.

### Patient post-visit survey

After the recorded visit, a brief face-to-face survey is administered to the patient participants. Items include socio-demographics data (age, gender, marital status, race and ethnicity, highest educational level attained, and insurance status), the SF-12, and other measures described in (sections Evaluation and measures and Exploratory outcome measures). The survey takes about 15 minutes. Patients then complete a 5–10 minute interview asking about their perspective on the content, adequacy, and clarity of communication about physical activity counseling.

Patients are compensated a total of $20 ($10 for participating in the audio recording portion and $10 for their time completing the survey and interview).

After the baseline assessment is completed for Group 1 clinicians and their corresponding patients, Group 1’s training intervention begins.

### Description of intervention

The intervention consists of four clinician training sessions, described below. Sessions 1–3 are conducted as a group; Session 4 is individually-based. Each session is facilitated by the principal investigator.

#### Curriculum for clinician training intervention

Clinicians are trained using didactic materials, skills/competency checklists, sample “scripts”, role play and cognitive rehearsal -- procedures regarded as effective techniques for communication training [37,50,51]. Standardized patients (actors) are used to portray realistic clinical situations, offer critique and feedback to each clinician, and assure that clinicians achieved the requisite skills.

#### Clinician training session 1

The objectives of Session 1 are to discuss 1) current evidence-based recommendations for physical activity, 2) contraindications to physical activity, 3) overview of the 5As, and 4) patient-centered communication and its use in physical activity counseling. Session 1 consists of a didactic presentation and an interactive group discussion. Consistent with self-determination theory and patient-centered communication, the discussion seeks to enhance clinicians’ understanding of their patients’ personal and social contexts for physical activity via counseling skills to elicit patient motivation for physical activity. The rationale for this is that understanding thepatients personal and social contexts for PA is consistent with supporting patient autonomy (by eliciting and acknowledging their feelings and perspectives about how their contexts might support or impede change) and competence (e.g. whether one’s own context influences their feelings of effectiveness in achieving their exercise goals.) The discussion also aims to enhance clinician motivation and competence to counsel by encouraging the group to discuss realistic ways to discuss physical activity despite the myriad challenges, barriers, and competing demands. All physical activity recommendations in the study are based on current physical activity national guidelines at the time of the intervention [52]. “To accumulate 30 minutes of moderate intensity physical activity over the course of most, preferably all, days of the week.”

#### Clinician training session 2

Session 2 consists of a brief review of the 5As, followed by an introduction to electronic tools developed to supplement the 5As and patient-centered communication for physical activity counseling using the practice electronic medical record. The tools are: 1) a History of Present Illness template, in which clinicians can view prompts to physical activity questions and answers, barriers, goals for change, and use pre-developed text to enter directly into the progress note , 2) a Social History box for entering physical activity data on type, duration, frequency, and intensity, 3) a Preventive Medicine page in the patient’s chart containing a generic activity prescription available for editing and customizing, 4) an Order Sets page in the chart, activated through one or two screen clicks for retrieving patient education handouts, and 5) a Referrals link in the chart, activated by one click, to make referrals to the community healthy living program. Clinicians receive a resource list with information on free or low cost community programs to consider as referral options for physical activity. Clinicians are taught how to use the Referrals Tab to refer patients to a community program for lifestyle change and physical activity that is available on-site at the health center. In order to support clinician competence and motivation to discuss physical activity, a variety of tools are provided to encourage flexibility in documentation of physical activity in the electronic health record and to accommodate different work styles. The local resource list is developed and provided to increase clinician confidence to counsel through awareness of available community options for physical activity. Additional file 1 shows screen shots of the five tools.

#### Clinician training session 3

The objective of session 3 is to implement the 5As including referral to an appropriate community resource if the patient was willing to go, while working with a standardized patient and observed by a peer. Session 3 also emphasizes the theoretical concepts of eliciting patients’ social context and being autonomy supportive by eliciting patients’ perspectives, preferences, and willingness to change. Clinicians are divided into pairs with each person taking turns conducting a visit with a standardized patient, debriefing with the standardized patient and the peer, and then repeating the cycle with a different standardized patient. Each standardized patient is trained according to case vignettes which have been developed and pre-tested with the principal investigator to portray common patient presentations and clinical scenarios for which physical activity discussion would be appropriate.

#### Clinician training session 4

The goal of session 4 is to reinforce and rehearse all of the aforementioned elements of the training and receive individual intensive feedback with a standardized patient. A standardized patient meets with each clinician individually to perform an assessment of skills acquired from the training according to a predefined checklist of core competencies. The standardized patient for session 4 is designed to portray a challenging patient with multiple medical and psychosocial conditions and barriers to exercise. The feedback emphasizes the importance of supportive listening to understand patients’ life contexts and challenges to activity, providing realistic problem-solving techniques to patients, and explicit mention of available community resources for physical activity. The standardized patient gives each clinician feedback on their 5As and PCC skills using a standardized checklist of competencies and open-ended, qualitative feedback.

### Post-intervention clinician assessment

The post-intervention clinician assessment occurs immediately upon completion of the intervention (or at approximately 6 months from the baseline assessment) and 6 months follow-up (or 12 months from the baseline) in the same manner described previously. Clinicians complete post-intervention and follow-up assessments of 15 audio-recorded office visits, divided across the two time points in the same manner as described in section 2.8. Group 1 clinicians complete a survey asking about the feasibility of the intervention, and individual brief interviews are conducted.

